#### Secondary endpoints

A generalized linear mixed model including group as the fixed effect and center and center*time period as random effects will also be used to compare each secondary endpoints between the two groups. For quantitative endpoints, the normality of the model residuals will be checked. In cases of non-normal distribution of residuals (except if a log-transformation could be applied to normalize the data), quantitative endpoints will be compared using a Mann-Whitney *U* test.

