## Methods/Design

### Design

BEST CUFF is a multicenter, cluster randomized crossover controlled and open-label trial performed in patients receiving mechanical ventilation in the ICU. Because tracheal intubation is an urgent procedure in ICU patients, the randomization was performed on the participating ICUs, and not on the patients. These ICUs were randomized into two balanced groups, according to an intervention sequence. Using this design, half of ICUs are randomized to use a PVC conical cuff (Fig. 1) in the first 1-month period and a PVC standard cuff (Fig. 2) in the second 1-month period. The other half of the ICUs will use the two interventions in the reverse sequence.

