**Fig. 2 Fig2:**
[figure not shown]
Standard tracheal cuff

Each ICU recruits distinct subjects during the repeated 2-month periods using the assigned intervention sequence, meaning that each intervention sequence started must be completed (Fig. 3).

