### Participating units

This study is currently conducted in ten French ICUs, including three located in university hospitals and seven in general hospitals.

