### Sample size

The main objective of this study is to demonstrate, in intubated critically ill patients, the superiority of conical cuff shape in reducing abundant microaspiration of gastric contents, compared with standard cuff shape (control group). Based on previous studies [13, 14], the expected incidence of abundant microaspiration of gastric contents is 50 % in control group. We assumed that the use of conical-cuffed tracheal tubes could reduce this incidence to 30 % (that is, an absolute and relative risk reduction of 20 % and 40 %, respectively). To detect this effect size, with a two-sided alpha risk of 5 %, and a power of 80 %, 90 patients would be required per group in a conventional parallel*-*group randomized trial. Since the experimental design is a cluster randomized crossover*,* we adjusted the study sample size to take into account the correlation between outcomes of patients within ICU (namely intraclass correlation coefficient, ICC) [33]. We did not take into account the inter-period correlation (correlation between different patients included within the same ICU but at different periods), in order to maximize the statistical power. Using the formula commonly used to plan a randomized cluster trial by considering each ICU as a pool of two independent clusters (one within each arm), assuming an ICC of 0.035 (corresponding to the upper quartile of ICC values from 31 primary care researches) [34], an expected total number of patients included per ICU of 30 patients, we calculated that 140 patients would be required per group. To account for an anticipated rate of 10 % of patients without any tracheal secretions, we planned to recruit a total of 312 patients.

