### Statistical analysis

Statistical analyses will be independently performed by the Biostatistics Department of University of Lille. Data will be analyzed using the SAS software (SAS Institute Inc, Cary, NC, USA), and all statistical tests will be performed with a two-tailed alpha risk of 0.05. Statistical analysis will be performed on an intention-to-treat basis. A detailed statistical analysis plan will be written and finalized prior to the database lock. The final report will be written, based on the CONSORT statement recommendations (Fig. 5).

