**Fig. 5 Fig5:**
[figure not shown]
Flow diagram of Best cuff trial according to CONSORT

Baseline characteristics will be compared between the two study groups. Quantitative variables will be expressed as mean (standard deviation), and median (interquartile range). Qualitative variables will be expressed as frequencies and percentages. Normality of distribution will be assessed graphically and using the Shapiro-Wilk test. Chi-square (or Fischer’s exact test), and Student *t*-test (or Mann Whitney test) will be performed to compare qualitative, and quantitative variables, as appropriate.

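### The fallback test for non-normal quantitative secondary endpoints drops the ICU and ICU-by-period terms, so its nominal 5 % level is not assured in this cluster crossover trial

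*Protocol article*

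**What the plan says.** The Design section states that "the randomization was performed on the participating ICUs, and not on the patients". The legend text on the period structure adds: "Each ICU recruits distinct subjects during the repeated 2-month periods using the assigned intervention sequence". There are ten ICUs (Participating units).

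The Sample size section says "we adjusted the study sample size to take into account the correlation between outcomes of patients within ICU", and the requirement rises from 90 to 140 patients per group.

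Under Statistical analysis, Secondary endpoints, every secondary endpoint is first assigned a generalized linear mixed model with group fixed and with ICU and ICU-by-period random. For quantitative endpoints the residuals are then checked. If they are not normal and a log transformation cannot repair them, "quantitative endpoints will be compared using a Mann-Whitney" U test. No stratification, cluster adjustment or rank-based mixed model is attached to that test. The general rule is that "all statistical tests will be performed with a two-tailed alpha risk of 0.05".

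The quantitative endpoints listed under Study outcomes are the per-patient proportion of amylase-positive aspirates, bacterial concentration, antimicrobial-free days, ventilation-free days and length of ICU stay.

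**The concern.** Skewness and dependence are separate problems. A skewed outcome gives no reason to stop allowing for the fact that patients in the same ICU and period resemble each other. As written, a residual check decides whether the analysis respects the unit of randomization.

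The Mann-Whitney null variance is derived for independent patients. In a cluster crossover, two departures pull in opposite directions. Correlation that is specific to an ICU-period inflates the variance of the arm difference and makes the test too liberal. A stable ICU effect cancels between arms, so ignoring it makes the test slightly conservative and costs power. The stated 5 % therefore need not be the actual level for any endpoint that takes this route.

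The article names the test explicitly. This is a method fixed in a form that does not fit the design, and not a detail left to a later analysis plan.

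**Working it through.** **Inputs from the article.** Ten ICUs; 30 patients per ICU, hence 15 per ICU and arm; ICC 0.035; inter-period correlation (IPC) not taken into account; each ICU handled as two independent clusters, one per arm; two-sided 5 %. **Assumed:** every non-zero IPC value, and the number of patients per ICU-period. The article gives no ICC or IPC for any quantitative secondary endpoint.

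**Step 1: reproduce the plan's sample size.**
- Unpooled two-proportion formula, 50 % against 30 %, 80 % power: (0.25 + 0.21) × (1.96 + 0.84)² / 0.20² ≈ 90.3. The stated 90 is reproduced.
- Design effect: 1 + (15 − 1) × 0.035 = 1.49. The pooled formula gives 93 per group, and 93 × 1.49 = 138.6, close to the stated 140.
- 140 / 0.9 = 155.6, rounded up to 156 per group, or 312 in total. This is exact.

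The planning therefore rests on a design effect of 1.49.

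**Step 2: actual level of a test that assumes independence.** Let m be the number of patients who share an ICU-period effect. The variance of the arm difference, relative to the variance under independence, is

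DE = (1 − ICC) + m × (ICC − IPC),

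and the actual two-sided level is 2 × (1 − Φ(1.96 / √DE)).

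**Step 3: planning device, m = 15, ICC 0.035.** The simulated column applies a plain Mann-Whitney test to log-normal outcomes in 10 ICUs, with 6,000 trials per row.

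| IPC | DE | Level by formula | Level simulated |
|---|---|---|---|
| 0 | 0.965 + 15 × 0.035 = 1.490 | 10.8 % | 10.25 % |
| half the ICC | 0.965 + 15 × 0.0175 = 1.228 | 7.7 % | 8.1 % |
| 0.8 × ICC | 0.965 + 15 × 0.007 = 1.070 | 5.8 % | 5.3 % |
| equal to the ICC | 0.965 | 4.6 % | 5.0 % |

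**Step 4: correlation acting only within the repeated 1-month periods, ICC 0.035.** Recruitment from June 2014 to October 2015 spans about 17 months. If ICUs stay open throughout (assumption), that is about 8 periods per arm, and 15 / 8 ≈ 2 patients per ICU-period. With 4 periods per arm it is 15 / 4 ≈ 4.
- m = 2, IPC 0: DE = 0.965 + 0.070 = 1.035, level 5.4 % (simulated 5.4 %, 4,000 trials).
- m = 4, IPC 0: DE = 0.965 + 0.140 = 1.105, level 6.2 %.
- Either m, IPC equal to the ICC: DE = 0.965, level 4.6 %.

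The range is about 4.6 to 6.2 %.

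**Step 5: sensitivity to a larger ICC.** ICC 0.10 is purely an assumption. With m = 15 the level is 20.6 % (IPC 0), 12.7 % (half the ICC) and 3.9 % (equal). With m = 2 to 4 it lies between 3.9 % and 8.6 % (at m = 4 and IPC 0, DE = 0.90 + 0.40 = 1.30). These figures show how strongly the level depends on unknown correlations. They are not a forecast for this trial.

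**The case against.** The strongest reply is that the large figure describes a simpler trial than this one. A level near 11 % needs correlation to persist across all of an ICU's months in one arm, yet vanish between that arm and the other arm's months interleaved with it. With short alternating periods the level stays close to 5 %. This stands, and it is why the result is given as a range.

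Also sound: the article does not assert that the inter-period correlation is zero. It sets that correlation aside for planning. The ICC of 0.035 is an upper-quartile value from primary care studies, used to size a binary primary endpoint, and its transfer to free-day counts or ICU stay is an assumption.

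Three stronger readings are tempting, and the document does not support them:
- A reader might infer that the fallback p-values are always too small, or that the error rate is doubled. Depending on the correlations, the test may be liberal, near nominal or slightly conservative.
- A reader might infer that most quantitative endpoints will end up with the fallback. The article contains no distributional data, and a log transformation may serve for ICU stay and bacterial concentration.
- A reader might extend the point to the baseline comparisons ("or Mann Whitney test) will be performed to compare qualitative, and quantitative variables, as appropriate"). They ignore clustering too, but they decide no efficacy claim and are a side matter here.

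The objection does not supply a reason for dropping the ICU terms when residuals are skewed. In none of these scenarios is the test matched to the design.

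**Conclusion.** The point holds, with limited reach. The fallback is not valid for the design in the sense that its level is not controlled: it depends on correlations that the test ignores and that the plan does not state for these endpoints. At ICC 0.035 the level runs from about 10.8 % under the planning device, through 7.7 % with the inter-period correlation at half the ICC, to 4.6 % when the two are equal. It is about 4.6 to 6.2 % if correlation is confined to the 1-month periods with an assumed 2 to 4 patients each.

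The exposure is greatest for endpoints that a log transformation is unlikely to repair because they are bounded or heavy at zero: the amylase-positive proportion, antimicrobial-free days and ventilation-free days. The primary endpoint and the binary secondary endpoints keep the mixed model. The fallback should be corrected before the analysis plan is finalized, but it does not threaten the main conclusion of the trial.

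**What to change.** Replace the Mann-Whitney fallback with a method that keeps the design. Options are:
- the same mixed model (group fixed; center and center*time period random) fitted to rank-transformed values;
- a proportional-odds mixed model with the same random effects, which suits the free-day counts;
- for amylase, a binomial mixed model on positive over total aspirates, with a patient-level random effect added because aspirates from one patient are correlated.

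The plan should also say whether time period means the calendar month or all months of one arm, because a month-level term would not absorb correlation that persists across an ICU's months in one arm. The calculations above do not test these replacements, so a short simulation of the chosen one with ten ICUs would be prudent.

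The Statistical analysis section foresees a detailed plan before database lock, so the change can be made there. It needs no new data. The cost is analysis plan wording, a different SAS call, and an effect measure on ranks or odds that is slightly less direct to interpret.

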## Discussion

Whether the conical cuff shape of the tracheal tube is efficient in reducing microaspiration of contaminated oropharyngeal and gastric secretions is unknown. Previous clinical studies reported conflicting results [24, 25] and had several limitations, precluding any definite conclusion. Our study is sufficiently powered to detect a significant difference in microaspiration of gastric contents between patients intubated with conical-cuffed tracheal tube and those intubated with standard-cuffed tracheal tubes. One of the strengths of this study is the use of quantitative measurement of pepsin as a marker of microaspiration. Pepsin is probably the most accurate, currently available, marker for microaspiration [9]. Whereas technetium-99 is the gold standard for the diagnosis of microaspiration of gastric contents [35], its use is not allowed outside the Radiology Department. The transport of critically ill patients outside the ICU has a considerable potential for misadventure and could be a life-threatening endeavor [36]. In addition, transport outside the ICU was identified as a risk factor for VAP [37]. Other markers for microaspiration, such as blue dye, and tracheobronchial colonization have several limitations, such as the qualitative measurement of microaspiration and the presence of confounding factors [9]. Alpha-amylase is a new marker for microaspiration of oropharyngeal secretions. Two recent studies [28, 38] reported promising results for its use in patients with aspiration pneumonia and in small cohorts of critically ill patients. However, our group found a moderate accuracy of alpha-amylase in diagnosing microaspiration compared with pepsin [29]. Further large clinical studies should validate its accuracy in patients with VAP.

We exclude patients with contraindication for enteral nutrition and those with gastrostomy because these factors might influence the primary outcome. We aimed to include patients early during invasive mechanical ventilation in order to increase the probability of them remaining under invasive mechanical ventilation and to have a complete period of 48 h during which tracheal aspirates are collected for pepsin and alpha-amylase measurements.

Nevertheless, we start collection of tracheal aspirates for pepsin measurements at least 12 h after intubation because this procedure is a well-known risk factor for microaspiration. As pepsin half-life is relatively short (3 to 4 h), this would probably allow a better interpretation of pepsin measurement results.

Subglottic secretion drainage is an effective measure in preventing VAP [39, 40]. However, this measure was not clearly recommended when our trial was designed, and its use was not generalized to all ICUs. In addition, one could argue that it is probably more accurate to evaluate the efficiency of these preventive measures, that is, the subglottic secretion drainage and conical shape, separately.

If the study hypothesis is confirmed, further studies should confirm the impact of conical cuff shape on the incidence of VAP.

## Trial status

Enrollment is ongoing. Inclusion started in June 2014. By March 2015, 201 patients had been included. Recruitment is expected to be complete in October 2015.

## Abbreviations

PVC: Polyvinyl chloride
VAE: Ventilator-associated event
VAP: Ventilator-associated pneumonia
